### Study Outcomes

The primary study outcome is the proportion of deaths from all causes during the first 7 days post randomization. Secondary outcomes include all-cause mortality at 30 days, hematoma expansion and recurrent ICH, brain infection, standard pharmacokinetic parameters (time to maximum plasma concentration [*T*_max_], *C*_max_, area under the curve, half-life [*t*_1/2_], clearance [CL], volume of distribution during terminal phase [*V*_z_], apparent terminal elimination rate constant [λ_z_]) determined at different times after MW189 administration, radiographic measures of edema during treatment and at the end of treatment for days 1–5, and measures of plasma and cerebrospinal fluid inflammatory and neuronal injury biomarkers during treatment and at the end of treatment for days 1–5. We will use a semiautomated threshold approach (range 44–100 Hounsfield units) to determine hematoma volume. Significant hematoma expansion will be defined as an increase between baseline and any follow-up CT scan of > 6 mL or > 33%. IVH volume will not be included in hematoma expansion. Recurrent ICH refers to the emergence of a new ICH following an initial episode of spontaneous ICH. It is subsequent spontaneous bleeding in the brain distinct from the initial event, typically occurring after a time frame of around 30 days or more. This is different from ICH expansion, which involves the enlargement of the initial bleed without the occurrence of a completely new bleeding event. Brain infection refers to infection present within the brain tissue and is evaluated based on the clinical symptoms, laboratory test results, and imaging findings. Radiographic measures of edema refer to the quantitative assessment of PHE and will be analyzed via both CT and magnetic resonance imaging (MRI) scans using semiautomated volumetrics with OsiriX software to compare the volume of edema between the two treatment groups. The primary imaging outcomes are absolute PHE and relative PHE and edema extension distance measured on brain CT scans performed at admission and at day 5 of the infusion. PHE measurements on MRI will be performed on the subset with MRI at baseline and at the end of the study. Group differences in edema volumes will be compared.

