Exploratory end points include clinical and functional outcomes collected at days 30, 90, and 180 (assessed using dichotomized modified Rankin Scale scores of 0–3 vs. 4–6, the National Institutes of Health Stroke Scale, the Montreal Cognitive Assessment, the Barthel Index, the Stroke Impact Scale, and the Center for Epidemiologic Studies-Depression scale) and participant status at 180 days from ICH, including serious AEs, AEs of special interest, hemorrhage expansion and recurrent ICH, infections, and mortality.

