### Data and Safety Monitoring

We have established an independent Data and Safety Monitoring Board (DSMB) to ensure the safety of enrolled participants. The DSMB review will occur every 6 months or independently after enrollment of 12, 30, 60, and 120 participants. Safety events that reach or exceed the prespecified threshold will trigger “suspend recruitment and review” by the DSMB to further investigate any presumed cause and impact of any events. Termination or suspension circumstances include determining unexpected or unacceptable risks, demonstrating significant efficacy, inadequate compliance to the protocol, incomplete or inconclusive data, meeting the primary end point, or establishing futility. The trial also includes monitoring events of special interest, such as phlebitis and infection. If 75% of all participants experience one or more of these events, the DSMB will be notified for review. This assessment will be conducted after the enrollment of the first ten participants. All clinical trial data, including all AEs, will be recorded on the case report form through day 5 or discharge, whichever occurs first.

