Medical history and admission information	X							
Concomitant medications review	X							
At randomization								
Vital signs	X							
Glasgow Coma Scale	X							
Baseline (premorbid) modified Rankin Scale (caregiver interview)	X							
Post randomization								
Research MRI					X			
Usual care clinical CT		X	X	X				
Research CT					X			
Therapy intensity level	X	X	X	X	X			
National Institutes of Health Stroke Scale	X	X	X	X	X	X		X
Glasgow Outcome Scale-Extended						X	X	X
Glasgow Coma Scale	X	X	X	X	X	X		X
Montreal Cognitive Assessment					X	X		X
Stroke Impact Scale-16					X	X		X
Barthel Index	X				X	X	X	X
Modified Rankin Scale						X	X	X
EQ-5D						X	X	X
Center for Epidemiological Studies–Depression						X	X	X
Concomitant medications review		X	X	X	X	X	X	X
Plasma biomarkers	X		X		X			
Cerebrospinal fluid biomarkers	X		X		X			
Pharmacokinetic blood samples	X	X	X		X			
Dosing	X	X	X	X	X			
Adverse events assessment	X	X	X	X	X	SAE/MEOI	SAE	SAE

CT, computed tomography; CTA, computed tomography angiography; ICH, intracerebral hemorrhage; MEOI, medical event of interest; MRI, magnetic resonance imaging; SAE, serious adverse events

Secondary and exploratory safety outcomes will be analyzed using appropriate linear or logistic regression models and will account for treatment group, age, GCS score, presence of IVH, ICH volumes, the timing of drug administration, and hematoma location. No imputation of missing safety end points will be used. Instead, sensitivity analyses will be performed, whereby participants with missing secondary safety data will be assumed to have had a safety event and then not to have had a safety event. The analyses will account for the variability in dosing and treatment duration, which can range from 2 to 10 doses depending on the date of discharge. This variability will be addressed through various approaches, such as categorizing participants into dose groups, treating the number of doses as a continuous variable, and calculating area under the curve that considers the dose and duration of the doses given. The point estimate of the proportion of total safety events and corresponding two-sided 95% confidence intervals will be calculated under both extreme scenarios to provide estimates of uncertainty in the presence of these missing data. SAS, STATA 17, and/or R software will be used for statistical analysis. Statistical significance will be set at *p* < 0.05.

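### The exploratory 180-day status end point includes special-interest events and infections, but Table 2 collects only serious events after the day-30 visit

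*Protocol article*

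**What the plan says.** **Study Outcomes, exploratory end points.** One end point is each participant's status 180 days after the ICH, made up of "serious AEs, AEs of special interest, hemorrhage expansion and recurrent ICH, infections, and mortality". Special-interest events and infections stand beside serious events as components of their own.

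**Table 2 (printed under Statistical Analyses).** The collection row reads "Adverse events assessment X X X X X SAE/MEOI SAE SAE". The columns are days 1 to 5, then day 30 (clinic), day 90 (phone) and day 180 (clinic). The footnote expands SAE and MEOI as two different abbreviations. CT is scheduled as usual care on days 2 to 4 and as a research scan on day 5; no imaging is scheduled at the three follow-up contacts.

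**Data and Safety Monitoring.** "The trial also includes monitoring events of special interest, such as phlebitis and infection". The same section ends: "All clinical trial data, including all AEs, will be recorded on the case report form through day 5 or discharge, whichever occurs first".

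**Study Outcomes, definitions.** For expansion: "Significant hematoma expansion will be defined as an increase between baseline and any follow-up CT scan of > 6 mL or > 33"%. Recurrent ICH is a new bleed, "typically occurring after a time frame of around 30 days or more".

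**The concern.** An end point can be reported only over the period in which its components are collected. Here the stated horizon is 180 days, but the schedule narrows at day 90 to serious events. Two listed components, special-interest events and infections, can both occur in nonserious form. A participant with a nonserious infection in month three would meet the wording of the end point and yet have no scheduled point at which it is recorded.

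Infection deserves care in this trial. The article names it as an event of special interest, and the introduction describes the drug as suppressing proinflammatory cytokine production. The results are also meant to inform a phase 2b/3 trial. A proportion labelled as 180-day that rests on serious-only reporting for most of that period could be taken as more complete than it is.

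**Working it through.** No figure in the plan is in dispute, so the check sets each component of the end point against the schedule.

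| Component of 180-day status | Days 1–5 | Day 30 | Days 90 and 180 |
|---|---|---|---|
| Mortality | collected | collected | collected |
| Serious AEs | collected | collected | collected |
| Special-interest events, nonserious | collected | collected if MEOI is this category | not scheduled |
| Infections, nonserious | collected | collected if counted as MEOI | not scheduled |
| Recurrent ICH | collected | collected as SAE | collected if reported as SAE |
| Hemorrhage expansion | scheduled CT | clinical scans only | clinical scans only |

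**Step 1: length of the serious-only period.** With the day-30 visit at day 30, (180 − 30)/180 = 150/180 = 83%. Follow-up Time counts visits from the last dose, whereas the end point counts from ICH. With dosing to day 5 the visit falls near day 35, and (180 − 35)/180 = 145/180 = 81%. The difference does not matter to the conclusion.

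**Step 2: what that share means.** It is a share of calendar time. Let L be the proportion of 180-day infections that occur after the day-30 visit and s the proportion of those that are nonserious. The plan as written misses s of the late infections and s × L of all 180-day infections. The article gives neither s nor L. Over an assumed range for s of 25% to 75%, one quarter to three quarters of the late infections would be missed. The loss over the whole 180 days is smaller in proportion to L, and would be small if few infections occur late.

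**Step 3: the MEOI assumption.** The article uses three terms (AEs of special interest, events of special interest, MEOI) and does not equate them. If MEOI is a different category, Table 2 has no code for nonserious special-interest events at any follow-up contact, and the uncovered period becomes (180 − 5)/180 = 175/180 = 97%. The gap is then wider, not narrower.

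**Step 4: the day-5 sentence.** For adverse events it largely agrees with Table 2: both place all-AE recording in the treatment days. The difficulty is its subject. Taken literally, stopping all trial data at day 5 or discharge would exclude the follow-up events in Table 2 and also deaths up to day 7 and day 30. That cannot be intended.

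**The case against.** The best defence is that this is a tiered safety scheme: all events during treatment, events of interest to day 30, serious events to day 180. With at most five days of dosing, serious-only late collection is a reasonable choice, and phlebitis, one of the two named special-interest events, is tied to infusion. The wording of questions at each contact is detail that an article may leave to the full protocol. Any loss applies to both arms, and blinded coordinators do the follow-up. All of this stands as a defence of the schedule. It does not remove the mismatch, because the article itself states both the wider end point and the narrower collection codes.

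Three stronger readings are tempting, and the document does not support them.

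- **That the article gives three conflicting adverse event windows.** The monitoring section does not say that serious events stop being recorded at day 5, and its all-AE window matches the marks on days 1 to 5. The conflict lies between Study Outcomes and Table 2; the monitoring sentence is badly worded.
- **That expansion at 180 days has no scan behind it.** Expansion is defined on any follow-up CT, so cumulative status can be filled from the scans to day 5 and from any later clinical scan. Expansion means enlargement of the first bleed, and the article places new bleeds at about 30 days or later. A routine late CT is not needed.
- **That 83% of events are lost.** Nothing in the article suggests that events are spread evenly over 180 days.

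**Conclusion.** The point holds in limited form. Study Outcomes promises special-interest events and infections to 180 days in addition to serious events; Table 2 schedules no collection of the nonserious ones after the day-30 visit. This rests on reading MEOI as the special-interest category, and the other reading widens the gap. The serious-only period is about 81% to 83% of the calendar window. The number of events missed cannot be derived from the document.

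The consequence is modest. The end point is exploratory, and 7-day and 30-day mortality are untouched. A reader might infer that late safety is not followed or that the arm comparison is biased. Neither follows: serious infections, deaths and clinically evident recurrent ICH should still be reported as SAEs, and the same schedule applies to both arms. What would be wrong is the 180-day label on a count collected under two different rules.

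**What to change.** 1. Reconcile Study Outcomes with Table 2 in one of two ways. Either add MEOI (special-interest events and infection) to the day-90 call and the day-180 visit, or define those components as through day 30, leaving SAEs (including serious infection and recurrent ICH) and mortality to day 180.
2. Use one term for the special-interest category throughout, or say how the three terms differ.
3. State that expansion is assessed on the acute-phase CTs through day 5 plus any later clinical scans.
4. Reword the closing sentence of Data and Safety Monitoring so that the day-5-or-discharge limit applies to the recording of all AEs and not to all trial data, with later collection as in Table 2.

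The cost is one question at two contacts that already take place, hence slightly longer contacts, or else a narrower stated end point. The remaining changes are wording. The primary analysis and sample size do not change.

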### Data and Safety Monitoring

We have established an independent Data and Safety Monitoring Board (DSMB) to ensure the safety of enrolled participants. The DSMB review will occur every 6 months or independently after enrollment of 12, 30, 60, and 120 participants. Safety events that reach or exceed the prespecified threshold will trigger “suspend recruitment and review” by the DSMB to further investigate any presumed cause and impact of any events. Termination or suspension circumstances include determining unexpected or unacceptable risks, demonstrating significant efficacy, inadequate compliance to the protocol, incomplete or inconclusive data, meeting the primary end point, or establishing futility. The trial also includes monitoring events of special interest, such as phlebitis and infection. If 75% of all participants experience one or more of these events, the DSMB will be notified for review. This assessment will be conducted after the enrollment of the first ten participants. All clinical trial data, including all AEs, will be recorded on the case report form through day 5 or discharge, whichever occurs first.

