### Randomization and Blinding

Randomization will be performed by a computer-generated randomization schedule that will assign participants 1:1 to either MW189 or placebo. The allocation sequence will be created and stored in a protected electronic data capture system. All providers and nurses participating in the treatment plan will be excluded from data and outcome analyses. The observers who assess the clinical outcomes will be blinded to the randomization results. A safety review will be performed in a blinded manner unless the data warrants unblinding because of the nature of any safety concerns. When unblinding is required, requests will be directly forwarded to the study’s unblinded statistician by the site investigator. To further maintain blinding during study drug administration, the IV equipment will be covered. Once the study drug is diluted, it must be stored at ambient temperature and protected from light until administration.

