### Sample Size Determination

The primary outcome of the study is to measure the proportion of participant deaths from any cause within the first 7 days after randomization. We anticipate that the mitigation of inflammation and edema will lead to fewer deaths in the MW189 arm during the acute phase. However, with an abundance of caution, we assume the placebo arm will have a similar number of deaths as compared to the MW189 arm. Therefore, we conducted a noninferiority power analysis using previously collected data from the Minimally Invasive Surgery Plus Alteplase for Intracerebral Hemorrhage Evacuation (MISTIE) III [27] and Antihypertensive Treatment of Acute Cerebral Hemorrhage II (ATACH-2) trials [28] to approximate the safety events that will be seen in the trial.

Considering a power of 80% and a one-sided 90% confidence interval, to test the null hypothesis of noninferiority with a tolerance limit of 12% and assuming a “worst-case” safety assumption of 10% rate of death in each arm, the sample size per group was estimated to be 57. We assume a low overall withdrawal rate in the first 7 days, and therefore 120 participants (60 per group) are required to evaluate the safety of MW189. This number also meets the estimated sample size for an 80% power and two-sided *α* to detect various assumed differences in PHE volume and maximum observed effect (*E*_max_) values in the interleukin-10 plasma cytokine response between treatment arms.

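### The notification trigger for phlebitis and infection pools both arms at 75%, so with balanced arms an excess confined to MW189 cannot reach it unless at least half of the placebo participants also have an event

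*Protocol article*

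**What the plan says.** The rule is in the protocol article, Methods, Data and Safety Monitoring. It first names the events: "The trial also includes monitoring events of special interest, such as phlebitis and infection". It then gives the threshold and denominator: "If 75% of all participants experience one or more of these events, the DSMB will be notified for review". The timing follows: "This assessment will be conducted after the enrollment of the first ten participants".

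Three other statements bear on how the rule works:

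- Randomization and Blinding: the schedule will "assign participants 1:1 to either MW189 or placebo". No blocking is described.
- Randomization and Blinding: "A safety review will be performed in a blinded manner unless the data warrants unblinding". The same section refers to an unblinded statistician for the study.
- Data and Safety Monitoring: "The DSMB review will occur every 6 months or independently after enrollment of 12, 30, 60, and 120 participants". A separate prespecified threshold leads to suspension of recruitment and review. Its value and the events it covers are not shown.

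The article states no by-arm or between-arm threshold for the events of special interest.

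**The concern.** A trigger on a pooled rate sees a drug effect only after it has been averaged with the placebo arm. At 1:1, half of the denominator receives saline, so the MW189 rate contributes at most 50 percentage points. The other 25 must come from placebo participants.

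An excess confined to the active arm is a plausible worry for these events. Study Intervention gives a pH of roughly 2.4 for the concentrate and a minimum of 3.0 after dilution, with 0.9% sodium chloride as placebo. The Introduction describes MW189 as a suppressor of proinflammatory cytokine overproduction and reports extremity pain and infusion site pain in the MW189 group in phase 1b. In a first-in-patient safety trial, the only printed criterion specific to these events should be able to respond to such an excess. If it stays silent, the silence should not be read as evidence that there is none.

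**Working it through.** **Inputs.** Threshold 75% of all participants, checked after ten are enrolled (Data and Safety Monitoring). Allocation 1:1 (Randomization and Blinding). Planned total: "120 participants (60 per group) are required to evaluate the safety of MW189" (Sample Size Determination). The 75% has no stated derivation, so there is no figure of the plan's to reproduce. The article gives no placebo rate for these events, so every placebo rate below is an assumption.

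**Step 1: the ceiling with balanced arms.** Let rM and rP be the proportions with at least one event on MW189 and placebo. The pooled rate is (rM + rP)/2. Setting (rM + rP)/2 ≥ 0.75 gives rM ≥ 1.5 − rP. Since rM cannot exceed 1, rP must be at least 0.5. With rM = 1 the pooled rate is:

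| Assumed placebo rate | Pooled rate if all MW189 participants are affected |
|---|---|
| 0% | 50% |
| 10% | 55% |
| 20% | 60% |
| 30% | 65% |
| 50% | 75% |

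**Step 2: whole participants.** Events needed = 0.75 × N, rounded up. Placebo events needed when all MW189 participants are affected = that number − N/2.

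| N | Events needed | Placebo events needed |
|---|---|---|
| 10 | 8 | 3 of 5 (60%) |
| 12 | 9 | 3 of 6 (50%) |
| 30 | 23 | 8 of 15 (53%) |
| 60 | 45 | 15 of 30 (50%) |
| 120 | 90 | 30 of 60 (50%) |

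**Step 3: chance of notification at ten, 5:5 split assumed.** With X_M ~ Bin(5, rM) and X_P ~ Bin(5, rP), P(X_M + X_P ≥ 8) = P(X_M=5)·P(X_P≥3) + P(X_M=4)·P(X_P≥4) + P(X_M=3)·P(X_P=5).

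- 80% versus 10%: 0.3277 × 0.00856 + 0.4096 × 0.00046 + 0.2048 × 0.00001 = 0.0030, or 0.3%.
- 90% versus 20%: 0.5905 × 0.0579 + 0.3281 × 0.0067 + 0.0729 × 0.0003 = 0.036, or 3.6%.

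**Step 4: chance at ten under simple randomization.** No blocking is stated, so the split may vary. Each participant then has an event with probability (rM + rP)/2, and the count is binomial with n = 10.

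- 80% versus 10%: mean rate 0.45. P(≥ 8) = 0.0229 + 0.0042 + 0.0003 = 0.027, or 2.7%.
- 90% versus 20%: mean rate 0.55. P(≥ 8) = 0.0763 + 0.0207 + 0.0025 = 0.0996, or 10%.

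The rise comes from lopsided splits. A split of 7:3 or more towards MW189 has probability 17.2%. A split of 8:2 or more has probability 5.5%, and in that case 8 affected MW189 participants reach the trigger with no placebo event.

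**Step 5: a larger count, in case the check is repeated.** At N = 30, 23 events are needed. With 15 per arm the chance is below 0.001% for 80% versus 10% and about 0.1% for 90% versus 20%. Under simple randomization it is 0.04% and 1.2%. Even with all MW189 participants affected and 20% on placebo, balanced arms give 5.8% at N = 10 and 0.4% at N = 30.

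**The case against.** The strongest reply is that this rule only adds a notification. The same section provides an independent DSMB, reviews every 6 months or at set enrollment counts, a separate suspension threshold, and suspension for unexpected or unacceptable risks. Unblinding is allowed when the data call for it. Closed DSMB reports may already be split by arm in the full protocol or the charter, which are not shown. This stands, and it limits the consequence. A reader might infer that nothing would reveal an arm imbalance, or that the trial is unmonitored. The article does not support either reading.

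A second reply is that a pooled count suits blinded monitoring and may be meant to flag a general tolerability or line-care problem. The article does not state the purpose. Pooling as such is defensible. The difficulty is the pairing of a pooled denominator with 75%, a level that an effect in one arm cannot reach in balanced arms.

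A third reply is that an unqualified claim that the trigger cannot fire is too strong. That is correct at ten participants, because no blocking is stated and a chance split can help. It would then fire partly because of the allocation. At larger counts such imbalance matters much less.

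Fourth, the placebo rate is unknown. The event list is open-ended, participants count if they have one or more events, and these are acutely ill patients with repeated infusions. A placebo rate of 50% or more would put the trigger within reach. The 10% and 20% used here are illustrations.

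Finally, a reader might see a contradiction between a check at ten and DSMB reviews "independently after enrollment of 12, 30, 60, and 120 participants". There is none. An event-specific check and a scheduled board review two participants later can coexist.

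**Conclusion.** The point holds for the rule as printed. With balanced arms, a pooled 75% cannot be reached by an effect confined to MW189 unless at least half of the placebo participants also have an event, or 3 of 5 at the look after ten. This follows from the stated threshold and 1:1 allocation alone.

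The probabilities rest on assumed rates and on how the first ten are split. Across the two rate scenarios and both allocation assumptions, the chance of notification at ten runs from 0.3% to 10%, so the trigger would stay silent at least 90% of the time despite a very large excess on MW189.

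The consequence is an insensitive notification rule. It is not a gap in oversight as a whole, since other DSMB safeguards are stated. It is worth correcting because it is the only printed criterion specific to these events.

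**What to change.** Have the unblinded statistician already named in the article tabulate the events of special interest separately for MW189 and placebo, and give the table to the DSMB in closed session. Base the notification on the by-arm figures, at a level the DSMB sets, and apply it at the early look and at each scheduled review. If a pooled count is kept as a blinded tolerability check, say that this is its purpose and that it is not meant to detect a difference between arms.

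The cost is one protocol sentence, a matching entry in the DSMB charter and a small amount of extra unblinded reporting. Study teams stay blinded, and neither the sample size nor the primary analysis changes.
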